#### 2.3.2. Recruitment of Participants and Informed Consent

In the participating schools, the research staff will recruit the participants visiting the selected classes and explaining the study to prospective adolescent participants. Adolescents who do not participate in the PE lessons due to any physical or mental diseases at the time of data collection would be excluded from the study. Only adolescents with signed parental consent will be eligible to participate.

#### 2.3.3. Sample Size Calculations

A minimum sample size of 300 participants will be needed to detect an odds ratio of 1.5 in the primary outcome (i.e., PA), assuming an alpha error of 0.05 and 80% of statistical power [51]. Therefore, 50 participants regardless of gender per school (6 schools) are needed. To account for the potential loss to follow-up of up to 50% participants regardless of gender (based on investigators’ previous experience due to the use of wearable devices), a total of 360 adolescents will be recruited (i.e., 120 participants per city). The groups randomization will be done at a 1:1 ratio at city level (i.e., from each city, 60 participants will be randomized to intervention and 60 to control groups).

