### 2.3. Procedure

#### 2.3.1. School Recruitment and Randomization

A list of all public high schools from each of the participating cities will be obtained from the educational government institutions (see Figure 3). The schools will be randomly selected in each city separately and a final ordered list will be created. The inclusion criteria for schools´ participation will be: (1) the school must have at least 2 class groups of 3rd grade of secondary education, (2) each class group must include at least 15 adolescents, (3) there must be at least 15 informed consents per class group, (4) the adolescents must have not taken part in other interventions to promote ACS or PA during the PACO study intervention period, and (5) the school must not offer bus transportation to the adolescents. If a school decides not to participate in the study, the same procedure will be carried out with the next selected school from the ordered list.

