PA will be measured objectively with a triaxial accelerometer (Actigraph wGT3X-BT, Pensacola, FL, USA) for 7 consecutive days, during waking time. Adolescents will be instructed to use an accelerometer attached to the waist on the right side of the body. Additionally, they will be instructed in the care of the device and it will be removed during water activities and sleeping time during night. Students will also complete an activity diary to record when the accelerometer is removed, the time when they wake up and go to sleep, as well as, the time when they go out from home to school. The Actilife software (Actigraph, v.6, Pensacola, FL, USA) will be used both for the initial configuration before the evaluations and for the data dump registered during the evaluation week. Accelerometers should be programmed with a frequency of 90 Hz and an epoch length of 15 s according to the recommendations for the sample of this study (adolescents) [70]. The final variables to analyse will be the daily minutes of light, moderate, vigorous, moderate to vigorous, and total PA.

In addition, we will also extract accelerometer data from specific times of the day for each participant, calculating the PA during commuting from home to school, commuting from school to home, in-school and out-of-school hours. Participants will carry a GPS (model Q STARZ BT-Q1000XT -Q STARZ International Co., Ltd. Taipei, Taiwan) on the left side of the body on the same belt of their accelerometer during the last two consecutive week days carrying the accelerometer.

Moreover, the PA will be self-reported through the questionnaire Youth Activity Profile, which provides a simple, low-cost, and educationally sound method that have already been calibrated and validated to accurately estimate children’s MVPA and sedentary behaviour at the group level [71,72]. A Spanish version of the Youth Activity Profile questionnaire was elaborated using a back-translation process and it has been shown to be a feasible and reliable questionnaire in Spanish adolescents [63]. The Youth Activity Profile questionnaire includes a total of 19 items, including 4 general items and 15 specific items divided into three sections: (1) activity at school, (2) activity out of school, and (3) sedentary habits. The final variables to analyse will be an average score ranging from 1 to 5 (lowest to highest) about the PA at school and PA out-of-school.

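### The sample-size paragraph is wrong as written: 300 pupils do not give 80% power for an odds ratio of 1.5 between two arms, and 360 recruited with 50% loss leaves 180, not 300.

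*Protocol article*

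**What the plan says.** Section 2.3.3 states: "A minimum sample size of 300 participants will be needed to detect an odds ratio of 1.5 in the primary outcome (i.e., PA"). The same sentence sets the type I error at 5% and the power at 80%. The next one makes clear that 300 is the total over both arms: "Therefore, 50 participants regardless of gender per school (6 schools) are needed". The paragraph then continues "To account for the potential loss to follow-up of up to 50% participants regardless of gender", a figure it attributes to the investigators' experience with wearable devices, and concludes that "a total of 360 adolescents will be recruited". Section 2.2 repeats 360, with 180 per arm.

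The paragraph gives no control rate, no sidedness and no allowance for clustering. Section 2.1 says that schools are randomised, one intervention and one control school in each of three cities. For accelerometer physical activity (PA), Section 4.2.1 says: "The final variables to analyse will be the daily minutes of light, moderate, vigorous, moderate to vigorous, and total PA". Section 6 compares the groups by ANCOVA.

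**The concern.** Three things look wrong on reading. An odds ratio of 1.5 is a modest effect, and 150 pupils per arm is far fewer than a comparison of two proportions usually needs for it. An odds ratio is also not the effect measure for an outcome in minutes per day. And going from 300 to 360 adds a fifth, which cannot absorb a loss of one half.

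What is at stake is how a null result is read. A reader who takes the paragraph at its word would treat a non-significant PA result as evidence against the intervention from a trial with 80% power for the effect it names. If the true power is well under half that, the result says much less.

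**Working it through.** **Inputs.** Odds ratio 1.5, alpha 0.05, 80% power, total 300, target 360 and loss up to 50% are from Section 2.3.3. The 1:1 allocation is from Sections 2.2 and 2.3.3. The control rate p1 is not given, so it was scanned from 0.5% to 99.5%. One reference point is 23.4%, the complement of the 76.6% insufficiently active adolescents in Section 1.1. Sidedness is not stated; two-sided is the default and one-sided is also shown.

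**Step 1: trying to reproduce 300.** The intervention rate is p2 = 1.5·o/(1 + 1.5·o), with o = p1/(1 − p1). With p̄ the mean of p1 and p2, the number per arm is

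n = [1.960·√(2p̄(1 − p̄)) + 0.842·√(p1(1 − p1) + p2(1 − p2))]² / (p2 − p1)².

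At p1 = 0.45, close to the most favourable rate, p2 = 0.551 and n = (1.386 + 0.592)² / 0.1010² = 383.4. That is 384 per arm, 768 in total.

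| Control rate | Total N, two-sided | Total N, one-sided | Two-sided power, 300 | Two-sided power, 180 |
|---|---|---|---|---|
| 20% | 1,070 | 842 | 32% | 21% |
| 23.4% | 970 | 764 | 34% | 22% |
| 45% | 768 | 604 | 42% | 27% |
| 50% | 776 | 610 | 41% | 27% |

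The minimum over the whole scan is 768 two-sided and 604 one-sided. The stated 300 is not reached anywhere. Power at 150 per arm and p1 = 0.45 is Φ[(0.1010·√150 − 1.386)/0.703] = Φ(−0.21) = 42%; one-sided it is 54%. With 300 pupils, 80% two-sided power is reached only for an odds ratio of about 1.9 at best, and about 2.0 at a 23.4% control rate.

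**Step 2: reading it as a continuous outcome.** Converting the odds ratio gives d = ln(1.5)·√3/π = 0.2235 SD. The total is 4·(1.960 + 0.842)²/0.2235² = 628.3, so about 629. With 300, power is Φ(0.2235·√75 − 1.960) = 49%. With 180, it is Φ(0.2235·√45 − 1.960) = 32%.

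**Step 3: the loss allowance.** This step uses only the document's own figures.

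- 360 × (1 − 0.5) = 180, or 30 per school against the 50 stated as needed.
- 1 − 300/360 = 16.7% is the loss that 360 can absorb.
- 300/(1 − 0.5) = 600 would be needed to keep 300 after 50% loss.

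**Step 4: clustering.** Steps 1 and 2 treat pupils as independent. The document gives no intraclass correlation (ICC), so 0.01 to 0.05 is an assumption. With 50 per school the design effect is 1 + 49·ICC = 1.49 to 3.45, and 300 pupils carry the information of about 201 to 87 independent ones. This ignores the further cost of having only three schools per arm.

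For a comparison of school means, the smallest difference detectable with 80% power is approximately (t₀.₉₇₅ + t₀.₈₀)·√(2·DE/(3m)) in SD units, with m pupils retained per school and DE = 1 + (m − 1)·ICC.

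| Degrees of freedom | m = 50, ICC 0.01 to 0.05 | m = 30, ICC 0.01 to 0.05 |
|---|---|---|
| 4 (unpaired) | 0.52 to 0.80 SD | 0.63 to 0.87 SD |
| 2 (paired by city, no variance gain) | 0.76 to 1.15 SD | 0.91 to 1.25 SD |

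All of these are well above 0.22 SD.

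**The case against.** The strongest reply is that 300 can be reached by other routes and that the source cited for the calculation is not available here. Two routes do get there. A logistic regression with odds ratio 1.5 per SD of a continuous predictor and a 20% event rate gives (1.960 + 0.842)²/(0.20·0.80·ln(1.5)²), about 299; but that is not a comparison of two arms. Converting the odds ratio to 0.2235 SD and adjusting for a baseline correlated about 0.72 with follow-up gives 628.3·(1 − 0.72²), about 303. This second route is closer to the planned ANCOVA. However, the document states neither the conversion nor the correlation, nor that baseline is the covariate, and the route still ignores schools. With 180 retained it gives about 58% power. So a reader might infer that no reading at all yields 80% power, and that goes too far. What stands is that the stated inputs do not yield 300 as a two-arm comparison.

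Three further inferences should be resisted.

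- The 50% is an upper limit tied to wearable devices. The 180 is therefore the worst case for accelerometer PA, and not necessarily the retained sample for cycling and active commuting, which come from questionnaires. The sentence still fails for PA, the outcome it names.
- The school criterion "there must be at least 15 informed consents per class group" might look like a contradiction of the 30 per class in Section 2.2. It is an eligibility floor below a target, and the two can coexist.
- The rarity of cycling to school might suggest a power failure there too, but the paragraph is sized on PA and claims no power for cycling.

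Finally, Section 7 lists the low sample size as a limitation. That softens the risk of misreading a null result, but leaves the 80% figure uncorrected.

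**Conclusion.** The point holds, and the paragraph should be corrected.

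The loss arithmetic needs no assumption beyond reading the 50% as the worst case that the target is said to cover: 180 remain, 60% of the stated minimum.

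The power statement fails over the whole range of control rates, one- or two-sided, for a two-arm comparison of independent pupils. The shortfall is at least a factor of about 2.6 two-sided (768/300) and 2.0 one-sided (604/300). Two-sided power with 300 is at most about 42% for proportions, or 49% on the converted mean difference without baseline adjustment. With 180 these become about 27% and 32%. Clustering lowers all of them by an amount that depends on an ICC the document does not give.

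The mismatch between an odds ratio and an outcome in minutes supports the point, because it leaves unclear what effect the trial was sized for.

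**What to change.** In Section 2.3.3:

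1. Withdraw the statement that 300 pupils give 80% power for an odds ratio of 1.5.
2. Correct the loss sentence to say one of two things: 360 recruited keeps 300 if loss is 16.7%, or 50% loss leaves 180 for PA.
3. Keep the six schools and state the PA difference they can detect, in minutes per day or SD, allowing for school clustering. Give the assumed ICC, the number retained per school and the degrees of freedom, and mark the figure as conditional on them. As an illustration, ICC 0.01 to 0.05, 30 to 50 retained per school and 4 degrees of freedom give about 0.5 to 0.9 SD. The figure is larger with 2 degrees of freedom if the analysis is paired by city and pairing removes no variance.

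This is a change of wording only, with no extra pupils or schools. The cost is that the stated power becomes much less favourable.

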## 1. Introduction

### 1.1. Active Commuting to School: Benefits, Prevalence and School-Based Interventions

The physical, psychological, and social benefits of meeting physical activity (PA) recommendations (i.e., 60 min of daily moderate-to-vigorous PA [MVPA]) have been well-documented in the scientific literature [1]. However, four out of five adolescents do not meet these MVPA guidelines [2]. Specifically, in Spain, 76.6% of adolescents between 11 to 17 years old are insufficiently active [2]. Since previous studies have shown that PA patterns in childhood track to adulthood [3], promoting regular PA levels in young people is a public health concern [4].

Active commuting to and from school (ACS) is defined as any walking or cycling to and from school; while passive commuting refers to the use of motorized vehicles as a mode of commuting, such as by car, bus, metro, train, or motorcycle, among others [5]. ACS in adolescents is a routine behaviour that is associated with higher levels of PA on schooldays [6,7,8], less time spent in sedentary pursuits [9] and has social and mental benefits [10]. Compared to walking, cycling to school leads to significantly higher physiological benefits, particularly regarding cardiorespiratory fitness, due to its higher PA intensity [6]. In addition, ACS also has environment and economic benefits [11]. Moreover, getting young people physically active during their trip between home and school is currently one of the main priorities of global policies, such as the Global Action Plan on Physical Activity 2018–2030, promoted by the World Health Organization [12], and the 2030 Agenda for Sustainable Development, promoted by the United Nations [13].

However, despite the well-known benefits associated with ACS, fewer than half of adolescents globally use ACS [14], with large variability across countries [9]. In Spain, about 50% of adolescents reported walking to school and only 0.3% reported cycling to school [15]. Although 68.2% of Spanish adolescents and young people aged 12 to 24 years already own a bicycle and 92.2% of them could ride a bicycle [16], less than 2% reported cycling to school [15,17,18,19]. Given that cycling to school tends to track from childhood to adolescence [20], along with its documented benefits, promoting this health-related behaviour should be a public health priority.

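### 300 pupils cannot give the stated 80% power for an odds ratio of 1.5: an unadjusted two-proportion comparison has at most about 42% two-sided or 54% one-sided, before clustering

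*Protocol article*

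**What the plan says.** Section 2.3.3 (Sample Size Calculations) gives the protocol article's only power statement: "A minimum sample size of 300 participants will be needed to detect an odds ratio of 1.5 in the primary outcome (i.e., PA". Alpha is set at 0.05 and the power claimed is 80%. The section cites an outside reference for the method.

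The next sentence fixes 300 as the total over both arms: "Therefore, 50 participants regardless of gender per school (6 schools) are needed". On allocation it says: "The groups randomization will be done at a 1:1 ratio at city level". With three intervention and three control schools, that is 150 pupils per arm.

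The section does not print a control-group rate, the sidedness of the test, the test itself or any allowance for clustering. The only related prevalence is in section 1.1: "in Spain, 76.6% of adolescents between 11 to 17 years old are insufficiently active". Section 4.2.1 defines accelerometer PA on a continuous scale: "The final variables to analyse will be the daily minutes of light, moderate, vigorous, moderate to vigorous, and total PA".

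**The concern.** An odds ratio of 1.5 is a modest effect, and 150 per arm is small for it. Even at the most favourable control rate, the two groups differ by only about 10 percentage points.

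The figures of 300 and 50 per school rest on this calculation. If the 80% is wrong, a null result could be read as good evidence against an effect of the stated size when the trial had far less chance of finding one.

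This is separate from the mismatch between an odds ratio and an analysis of minutes. The shortfall remains if PA is dichotomised to suit the odds ratio, and also if the odds ratio is converted to a difference on a continuous scale.

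**Working it through.** **Inputs from section 2.3.3:** 300 in total, 1:1, so n = 150 per arm; odds ratio 1.5; alpha 0.05; stated power 80%.

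**Not printed:** the control rate p1 (scanned from 0.001 to 0.999) and sidedness (both tried). As one reference value, section 1.1 implies p1 = 1 − 0.766 = 0.234.

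**Formulas (two proportions, unadjusted, pooled variance under the null)**
- p2 = 1.5·p1 / (1 + 0.5·p1)
- Power = Φ{ [ |p2 − p1|·√n − z_α·√(2·p̄(1 − p̄)) ] / √[ p1(1 − p1) + p2(1 − p2) ] }, where p̄ is the mean of p1 and p2, and z_α is 1.960 two-sided or 1.645 one-sided.

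**Step 1. Try to reproduce 80%.** Over the whole scan, power at 150 per arm peaks at p1 = 0.449:
- p2 = 0.550, difference 0.101.
- Two-sided: Φ[(0.101 × 12.247 − 1.960 × 0.7071) / 0.7035] = Φ(−0.21) = 41.6%.
- One-sided: 54.2%.

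Other two-sided methods give similar maxima: arcsine 41.8%, Wald test on the log odds ratio 41.6%, simulation of the pooled z-test 43.9%. The stated 80% is not reproduced.

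**Step 2. Other control rates, two-sided, 150 per arm**

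| Control rate | Intervention rate | Power | Total N for 80% |
|---|---|---|---|
| 0.10 | 0.143 | 20.5% | 1,822 |
| 0.20 | 0.273 | 31.6% | 1,070 |
| 0.234 | 0.314 | 34.3% | 970 |
| 0.45 | 0.551 | 41.6% | 768 |
| 0.60 | 0.692 | 38.6% | 842 |

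The smallest total N for 80% at any control rate is 768 two-sided and 604 one-sided.

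**Step 3. Use every recruit.** With all 360 and no loss (180 per arm), the maximum is 48.3% two-sided and 60.8% one-sided.

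**Step 4. Read the odds ratio on a continuous scale.** d = ln(1.5)·√3/π = 0.4055 × 0.5513 = 0.224. Two-sided power without covariate adjustment is Φ(0.2235 × √75 − 1.960) = Φ(−0.02) = 49.0%; 80% needs 630 in total. An ordinal proportional-odds reading gives at most 52.7% and needs at least 573.

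**Step 5. What 300 can detect.** At 80% power, two-sided and before clustering, the smallest detectable odds ratio is about 1.92 at the best control rate and about 2.03 at 0.234.

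**Step 6. Clustering.** Schools are the randomized units (section 2.1). The design effect with 50 per school is 1 + 49 × ICC. The documents give no ICC, so a range is assumed:

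| Assumed ICC | Design effect | Effective n per arm | Maximum two-sided power |
|---|---|---|---|
| 0.01 | 1.49 | 100.7 | 29.8% |
| 0.02 | 1.98 | 75.8 | 23.6% |
| 0.05 | 3.45 | 43.5 | 15.3% |

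**The case against.** The strongest reply is that the test, sidedness and control rate are not printed and that the cited reference may contain them. It would be wrong to say that every input is on the page. That part stands, but it does not save the 80%: the maximum over all control rates, one-sided as well as two-sided, is far below it.

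A second reply is that 300 came from a different calculation. Three readings come close:
- 300 per arm, one-sided, at the best control rate gives 79.8%. Section 2.3.3 makes 300 the total.
- An odds ratio per SD of a continuous predictor at 20% prevalence needs about 298 pupils. The trial compares two randomized groups, so that formula does not apply.
- An ANCOVA on the converted difference of 0.224 reaches 80% if the covariate-outcome correlation is about 0.72. ANCOVA is the planned method (section 6), but no such correlation is stated.

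None of these validates the printed claim. They do show that a mis-specified effect measure may be the cause, which cannot be settled without the reference.

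A reader might infer that 42%, or 34%, is the trial's real power, or that the trial would necessarily miss its target effect more often than not. The documents do not support this. The 42% is a ceiling for an unadjusted two-sided test of two proportions, which is not the planned PA analysis; one-sided, the ceiling is above one half. The 34% uses a national figure for ages 11 to 17 that section 2.3.3 does not invoke.

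The discussion (section 7) does list the small sample as a limitation, but it does not correct the power figure.

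**Conclusion.** The stated power is wrong as written. With 150 per arm and an odds ratio of 1.5, an unadjusted two-proportion comparison at alpha 0.05 gives at most about 42% power two-sided and 54% one-sided, whatever the control rate. At least 768 pupils would be needed for 80% two-sided, about 2.6 times the printed 300 (768/300 = 2.56). The continuous-scale reading gives about 49%.

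These figures assume individual randomisation, no loss and no covariate adjustment. Covariate adjustment could raise power, but the document states no correlation to support that. Clustering works the other way and is certain to matter if the intracluster correlation is positive; the 0.01 to 0.05 range used here is an assumption.

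The conclusion is that the 80% claim cannot stand for an odds ratio of 1.5, not that the trial's actual power is a particular lower number.

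**What to change.** In section 2.3.3, withdraw the claim of 80% power for an odds ratio of 1.5. Replace it with the power, or the smallest detectable effect, that the planned size gives, and state:
- the effect measure that matches the planned PA analysis;
- the control rate (if PA is dichotomised) or the SD and any assumed baseline correlation (if minutes are analysed);
- the sidedness of the test;
- a range of intracluster correlations and the resulting design effect.

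As a reference point, 300 pupils detect an odds ratio of about 1.9 to 2.0 at 80% power, two-sided, before clustering, and only a larger one after it. Printing 34% to 42% as the new power without a clustering caveat would itself overstate it.

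If 300 came from another effect measure, state that measure and its inputs instead.

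The cost is rewriting one paragraph and accepting a less favourable stated power. Recruitment need not change.

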### 2.2. Study Population

A total of 360 adolescents aged 14–15 years (3rd grade of secondary education; hereinafter called 3rd grade) from 6 high schools located in 3 Spanish cities will be recruited (see Figure 2). The randomization process is presented in the Figure 2. Within each city, 2 high schools, randomly selected and allocated to intervention or control treatment, will participate in the study. Within each secondary school, two class groups of approximately 30 participants each will be invited to participate and allocated to intervention or control conditions. The final target sample will comprise 360 adolescents (120 adolescents per city; 180 adolescents in the intervention and 180 in the control group).

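### The target of 360 is said to cover loss of up to 50% from a required 300, but it covers at most 16.7%; at the stated ceiling 180 pupils remain

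*Protocol article*

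**What the plan says.** The sizing is in section 2.3.3 (Sample Size Calculations) of the protocol article, which makes three statements in sequence:

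- The requirement: "A minimum sample size of 300 participants will be needed to detect an odds ratio of 1.5 in the primary outcome (i.e., PA"). The test level is 5% and the power 80%. Spread over the schools, this becomes: "Therefore, 50 participants regardless of gender per school (6 schools) are needed".
- The allowance for loss: "To account for the potential loss to follow-up of up to 50% participants regardless of gender". The text bases this on the investigators' earlier experience and attributes it to wearable devices.
- The target that is meant to follow: "a total of 360 adolescents will be recruited (i.e., 120 participants per city").

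Section 2.2 (Study Population) repeats the target: "The final target sample will comprise 360 adolescents", split 180 and 180 between the arms. It builds this from two classes of about 30 pupils in each of six schools. The Abstract gives the same 360, and Table 2 uses it as the target against which reach is measured. The Discussion lists low sample size as a limitation but does not return to the calculation. No section gives a larger recruitment figure or a smaller loss figure.

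**The concern.** The paragraph presents 360 as the result of inflating 300 for loss of up to half the sample. The inflation is only 60 pupils. A sample that may halve cannot be protected by adding a fifth.

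A reader of section 2.3.3 would conclude that the trial keeps its stated power even if half the pupils yield no usable data. If the loss came anywhere near that ceiling, a null result on physical activity would be read as coming from a trial with 80% power, when the analysed sample was well below the plan's own minimum. Because the loss is attributed to wearables, it would bear mainly on accelerometer-measured physical activity, one of the primary outcomes.

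**Working it through.** **Inputs, all from section 2.3.3:** required minimum 300; 6 schools; loss up to 50%; recruitment target 360; alpha 0.05; power 80%. Sidedness, a control-group rate and an allowance for randomisation by school are not stated there.

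**Step 1. Figures that reproduce.** 50 × 6 = 300. 120 × 3 cities = 360. Section 2.2 reaches the same number as 6 schools × 2 classes × 30 = 360.

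**Step 2. Can 360 be derived from 300 and 50%?**

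- Correct inflation, N/(1 − d): 300/(1 − 0.50) = 600.
- Common shortcut, N × (1 + d): 300 × 1.50 = 450.

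Neither gives 360.

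**Step 3. What loss does 360 cover?**

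- 1 − 300/360 = 0.167, so at most 16.7%.
- 360/300 = 1.20, so the target matches the shortcut rule with 20% loss. By the correct rule, 20% loss would need 300/0.80 = 375.

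**Step 4. What remains at the stated ceiling?** 360 × (1 − 0.50) = 180, which is 90 per arm or 30 per school, against 50 per school required. 180/300 = 60%.

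**Step 5. Illustration of the effect on power.** Take as given that 300 analysed gives 80% power, two-sided 5%, with no clustering. The noncentrality at 300 is 1.960 + 0.842 = 2.802 and scales with √n, so power at n analysed is Φ(2.802 × √(n/300) − 1.960).

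| Loss | Analysed of 360 | Power |
|---|---|---|
| 10% | 324 | 82.9% |
| 16.7% | 300 | 80.0% |
| 20% | 288 | 78.4% |
| 30% | 252 | 72.8% |
| 40% | 216 | 66.2% |
| 50% | 180 | 58.3% |

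For the last row: 2.802 × √0.6 = 2.170, and Φ(2.170 − 1.960) = 0.583.

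**Step 6. Why step 5 is only an illustration.** Its premise does not reproduce. A two-sided comparison of two proportions at an odds ratio of 1.5 needs the fewest pupils at a control rate near 0.45. There the other rate is 0.551, and the usual formula gives 384 per group, or 768 in total. Other control rates need more. One-sided, the smallest total is 604. Converting the odds ratio to a standardised difference (ln 1.5 × √3/π = 0.224) gives 630 two-sided. A logistic formula per standard deviation of a continuous predictor gives smaller totals: about 191 at an assumed event rate of 0.5, or 266 at 0.234 (the complement of the 76.6% insufficiently active in the Introduction). That is not this trial's two-group comparison. Section 2.1 also makes the school the unit of randomisation, and the calculation mentions no allowance for that. These points would lower power further, so they do not rescue 360. They do mean that the percentages in step 5 are not estimates of this trial's power.

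**The case against.** Four replies deserve weight.

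*The 50% is a ceiling, not a forecast.* This stands. A reader might infer that the investigators expect to lose half the sample and so that the trial will run at about 58% power. The text supports neither: it speaks of potential loss up to that level, and the 58% rests on a base figure that does not reproduce. The ceiling does not remove the contradiction, because the sentence says that 360 accounts for loss up to it.

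*The 50% may be the slip.* Plausible. The target is exactly 300 × 1.20 and also exactly two classes of 30 in six schools, so it may come from a smaller loss figure or from logistics. If loss were 20%, 288 would remain, a modest shortfall. The document does not say which figure is wrong, so the correction must allow for both.

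*The outcome that drives the sizing is not pinned down.* Section 2.3.3 names only physical activity. Section 4.2.1 lists accelerometer minutes and a self-reported activity questionnaire under that heading. That the loss falls on the very variable used for sizing is a reasonable inference from the reference to wearables, but it is not stated.

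*An article condenses the full protocol.* That would excuse a missing detail. Here all three figures are printed in one paragraph and disagree.

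**Conclusion.** The contradiction is real and depends on no unstated input: 300 required, up to 50% loss and 360 recruited to cover that loss cannot all hold. The target covers at most 16.7% loss, a third of the stated ceiling. At the ceiling it leaves 180 pupils, 60% of the plan's own minimum. Above 16.7% loss the stated 80% power is not delivered even if the base calculation is accepted.

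The size of the power shortfall is less certain. The fall from 80% to about 58% at the ceiling assumes that 300 gives 80% power, a two-sided 5% test and no clustering, and the first of these could not be reproduced. It shows the direction and rough scale of the problem, and should not be quoted as the trial's power. Nor does it follow that the trial must recruit 600; that holds only if both the 300 and the 50% are kept as they stand.

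**What to change.** Correct section 2.3.3, with no extra enrolment:

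1. State that 360 recruits allow for at most 16.7% loss from a requirement of 300.
2. If up to 50% loss of wearable data is the intended ceiling, say that as few as 180 pupils may be analysable for accelerometer physical activity. Restate the power, or the detectable effect, over the plausible range of loss. Recompute it from stated inputs (outcome definition, control-group rate, sidedness, allowance for randomisation by school) and do not scale it from the 300.
3. If 50% was a misstatement, replace it with a loss rate that 360 covers, and give the reason for it.
4. Give the expected loss for the questionnaire outcomes separately, because the 50% is attributed to the devices.

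The cost is one reworded paragraph and one recalculation. The drawback is that the stated power will look less favourable. Recruiting more pupils would be another way to resolve the conflict, but the correction does not require it.
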